### Procedures

All procedures described in this study were approved by the Ethics Committee of the Autonomous Community of Aragón. Changes to this original study protocol (current protocol version number 2; May 2, 2025) will be communicated to the aforementioned Ethics Committee for their approval.

Physicians and nurses working in the long COVID-19 unit will invite patients to participate in the study. Participants who are interested in the study will receive a document containing a QR code to access the online Qualtrics platform, where they can read and electronically sign the informed consent form. After signing the online document, participants will receive a numerical code to preserve their anonymity in subsequent online assessments, and will then complete the Overall Depression Severity and Impairment Scale (ODSIS; [24,25]) and the Overall Anxiety Severity and Impairment Scale (OASIS; [25,26]) to assess the presence of depressive and/or anxiety symptoms that helped the research team to determine whether they meet the initial eligibility criteria.

Participants who do not meet the ODSIS and OASIS criteria will receive an email thanking them for their interest in the study and informing them that they do not meet the initial eligibility criteria. In contrast, participants who meet the cutoff criteria for anxiety and depressive symptoms (ODSIS ≥ 7 and/or OASIS ≥ 8) will be contacted by telephone by the psychologist responsible for conducting the initial clinical interview and the subsequent psychological UP-based program. During this call, the psychologist will confirm that the participant is interested in taking part in the study and agrees to the conditions of the intervention (i.e., the possibility of being assigned to the waiting list control group, participation in the psychological intervention in an online group format, agreement with the assessment schedule, and provision of hair samples for cortisol/cortisone analysis). Once it is confirmed that the participant understands the study’s conditions and procedures, an online session via videoconference will be scheduled to conduct a clinical interview to determine the presence of an emotional disorder.

After confirming the presence of at least one emotional disorder according to the Anxiety and Related Disorders Interview Schedule for DSM 5 (ADIS-5; [27]), participants will complete the online pre-treatment assessment protocol and will then be informed by email of their group assignment (either the experimental or the waiting list control group). Randomization to the experimental or group condition will be conducted by an independent researcher who will consult the pre-generated randomization sequence. The psychologist will also be informed of the assigned group to facilitate the management and organization of the UP-based experimental group intervention.

Participants in the experimental group will be required to complete an in-person additional assessment before they can begin the program. Accordingly, individuals assigned to the experimental group will meet in Zaragoza with a member of the research team to complete the neuropsychological and cognitive tests and to provide a hair sample for subsequent cortisol/cortisone analysis (secondary objective of this study). After these assessment point, participants will receive the UP-based psychological intervention in 12 online group sessions, each lasting 2 hours. Given that long COVID-19 patients often report cognitive difficulties [28] a break of approximately 10 minutes will be scheduled midway through each session. After the intervention, participants will complete the online post-treatment assessment protocol, which will include the measures administered at pre-treatment and a satisfaction questionnaire. Follow-up online assessments will also be conducted at three, six and twelve months after the intervention. At these time points, a group online session will be scheduled to monitor progress and reinforce the emotion regulation skills learned during the UP psychological program. At the three and twelve-month follow-up assessments, participants will repeat the in-person assessment to complete the neuropsychological and cognitive tests and to provide the hair samples for cortisol/cortisone analyses. Participants will receive email reminders for these appointments.

In the case of participants who will be assigned to the waiting list control group, they will remain on the waiting list for 12 weeks and will not receive any psychological intervention. After this waiting period, they will complete the post-treatment assessment protocol and will then be enrolled in the experimental group following the same procedures previously described for this condition.

### Outcomes

As previously explained in the procedure section, the assessment protocol will include evaluations carried out via videocall, as well as in-person sessions and the completion of online surveys through the Qualtrics platform. Following the SPIRIT recommendations [22], Fig 1 presents the questionnaires administered at each time point as well as the administration format. In the following section, we briefly describe the questionnaires that will be administered.

**Fig 1 pone.0342908.g001:**
[figure not shown]
Participant timeline. Note: ADIS-5: Structured interview for anxiety disorders and related disorders; ODSIS: Overall Depression Severity and Interference Scale; OASIS: Overall Anxiety Severity and Interference Scale; MFE: Memory Failures of Everyday; MEDI: Multidimensional Emotional Disorders Inventory; DERS: Emotional Regulation Difficulties Scale; EQ-5D: EuroQol; DTS: Distress Tolerance Scale; PSS; Perceived Stress Scale; CSQ-8: Client Satisfaction Questionnaire; MoCA: Montreal Cognitive Assessment; WAIS-III: Digit Symbol subtest-Wechsler Adult Intelligence Scale-III; WAIS-IV: Digit subtest from Wechsler Adult Intelligence Scale-IV.

#### Eligibility criteria and sample characteristics: Online videocall assessment.

Anxiety and Related Disorders Interview Schedule for DSM-5 (ADIS-5) [27]: this interview will serve to determine whether participants meet criteria for an emotional disorder. This interview allows us to assess major depressive disorder, dysthymia, panic disorder, agoraphobia, obsessive-compulsive disorder, generalized anxiety disorder, post-traumatic stress disorder, social anxiety disorder, hypochondria, and adjustment disorders. In our study, participants showing symptoms consistent with anxiety or depressive disorders “not otherwise specified” will also be considered for inclusion in the study.Sociodemographics: the research team has developed an *ad hoc* questionnaire to obtain sociodemographic data from participants. Thus, information about sex, age, place of residence, marital status, number of children, employment status, income, lifestyle habits (sleep, smoking, alcohol, physical activity, diet) will be collected at pre-treatment.Long COVID-19 questionnaire: participants will be asked about their COVID-19 and long COVID-19 history, including questions regarding the number and dates of COVID-19 infections, the number and dates of COVID-19 vaccine administrations, the date of long COVID-19 diagnosis, and physical symptoms related to COVID-19 (from their first infection and at the present).

#### Primary outcomes: Online survey assessment.

Overall Depression Severity and Interference Scale (ODSIS) [24,25]: depressive symptoms are assessed across five items evaluating frequency, intensity, severity, and interference of symptoms. Scores range from 0 to 20 points, with higher scores denoting greater depressive symptoms severity. While the Spanish validation of the questionnaire established a cutoff score of 10 points [25], in this study, and similar to previous research [29], the cutoff has been reduced to 7 points to ensure that all participants who may be experiencing depressive symptoms are thoroughly assessed for eligibility and can benefit from the psychological intervention. Thus, ODSIS cut-off was established at approximately half standard deviation below the mean scores obtained in the Spanish validation of this questionnaires (mean=9.87, *SD*=5.14) [25].Overall Anxiety Severity and Interference Scale (OASIS) [25,26]: this instrument measures anxiety symptomatology across five items assessing frequency, intensity, severity, and interference of symptoms. Total scores vary from 0 to 20 points; higher values indicate more severe anxiety symptoms. As explained in the section describing the depression questionnaire (ODSIS), in this study the cutoff score for the OASIS has been reduced to 8 points, taking into account the mean and standard deviation reported in the Spanish validation (mean=10.45, SD=4.49) [25]. This threshold corresponds to approximately half standard deviation below the Spanish mean, a criterion that allows participants with subclinical anxiety symptoms to be assessed and, if they met criteria for an emotional disorder, to participate in the study.

#### Secondary outcomes: Online survey assessment.

Memory Failures of Everyday (MFE) [30,31]: the scale assesses how frequently individuals experience forgetfulness or memory lapses in everyday situations. It comprises 28 items and includes three factors: forgetting activities (i.e., failing to remember tasks or where objects are placed; maximum score: 20), difficulties recognizing places or people (maximum score: 12), and problems with communication monitoring and control (i.e., following a story, forgetting words or repeating stories among others; maximum score: 24). Higher scores in each subfactor indicate greater memory failures.Multidimensional Emotional Disorders Inventory (MEDI) [32,33]: this measure includes 49 items designed to assess the transdiagnostic profile of emotional disorders. It covers nine dimensions: neurotic temperament (5 items), positive temperament (5 items), depressed mood (5 items), somatic anxiety (5 items), arousal/activation (5 items), social anxiety (5 items), intrusive cognitions (6 items), traumatic re-experiencing (5 items), and avoidance (8 items). As shown, the number of items per dimension ranges from 5 to 8. Dimension scores are obtained by summing the corresponding item scores, resulting in total scores ranging from 0 to 40, 0 to 48, or 0 to 64, depending on the dimension. Higher scores reflect higher levels of that dimension.Difficulties in Emotion Regulation Scale (DERS) [34,35]: this instrument consists of 28 items that assess difficulties in emotion regulation across five subscales: lack of control (9 items), rejection (7 items), interference (4 items), inattention (4 items), and emotional confusion (4 items). It is also possible to obtain a global emotion dysregulation score by summing the scores of all items. Higher scores indicate greater difficulties in regulating emotions.EuroQol (EQ-5D) [36,37]: this questionnaire is used to evaluate participants’ health-related quality of life. It includes five items, each assessing one dimension of quality of life (i.e., mobility, self-care, usual activities, pain or discomfort, and anxiety or depression). In addition, this measure includes a visual analogue scale (VAS) on which respondents rate their overall health from 0 to 100. Higher scores on the VAS indicate better perceived health status.Distress Tolerance Scale (DTS) [38]: this scale assesses distress tolerance across 15 items, covering the following dimensions: (1) Tolerance (i.e., the perceived ability to withstand emotional distress; 3 items); (2) Appraisal (i.e., the subjective evaluation of distress; 6 items); (3) Absorption (i.e., the extent to which attention is captured by negative emotions; 3 items); and (4) Regulation (i.e., the strategies used to alleviate distress; 3 items). A global distress tolerance score can be obtained, with total scores ranging from 15 to 75. Higher scores indicate greater tolerance to distress.Perceived Stress Scale (PSS) [39,40]: this scale includes 14 items that assess the extent to which individuals have experienced stress in their daily lives during the past month. The authors of the Spanish validation proposed a shorter 10-items version of the PSS, which will be used in the present study. Total scores range from 0 to 40, with higher scores reflecting greater levels of perceived stress.Adaptation of Client Satisfaction Questionnaire (CSQ-8) [41]: while the original version of this questionnaire is composed of 8 items, in this study 6 of these items will be used to assess participants’ satisfaction with the intervention. These items cover (1) perceived quality of the program, (2) fulfillment of expectation, (3) likelihood of recommending the program, (4) perceived usefulness of the techniques, (5) general satisfaction with the program, and (6) willingness to participate in similar interventions in the future. An additional item will be included to evaluate any discomfort elicited by the intervention.Qualitative satisfaction reports: to capture participants’ qualitative feedback, five open-ended questions will be also presented: (1) Are there topics you would like to see included that were not addressed? (2) Is there any content you consider unnecessary and would remove? (3) Was the program duration (12 sessions of 2 hour each) sufficient? (4) How satisfied are you with the online, group format of the program? (5) Please share any additional concerns or comments regarding the program.Evaluation questionnaire of the UP modules (*ad hoc*): seven questions will be included in the satisfaction questionnaire to assess the perceived satisfaction with the UP-based psychological intervention. A general question about the usefulness of the UP for improving emotional regulation was first presented. Then six specific items will be shown to evaluate the perceived usefulness of each technique learned during the UP program. Total scores for each item ranges from 0 to 10 with higher scores indicating greater satisfaction with the intervention.

#### Secondary study objective: Face-to-face assessment.

Montreal Cognitive Assessment (MoCA) [42]: this neurological test will be used to obtain a score of the overall level of cognitive abilities. It assesses several cognitive domains, including visuospatial skills, memory, working memory, attention, concentration, language, executive functions, and orientation. The maximum total score is 30 points. Scores between 26 and 30 may be interpreted as indicative of normal cognitive functioning, whereas scores of 25 or below suggests the presence of cognitive impairment.Digit Symbol subtest-Wechsler Adult Intelligence Scale-III (WAIS-III) [43]: this cognitive test assesses psychomotor speed, sustained attention, and incidental learning and is a paper-and-pencil subtest of the Wechsler Adult Intelligence Scale–III. Participants are required to match digits (1-9) with their corresponding symbols as quickly as possible within a 120-second time limit. The number of correctly matched symbols constitutes the matching score (maximum score = 133). Immediately afterwards, incidental learning is assessed through an untimed cued-recall task (maximum score = 18) and an untimed free-recall task without digit cues (maximum score = 9).Digit subtest from Wechsler Adult Intelligence Scale-IV (WAIS-IV) [44]: this subtest assesses verbal short-term and working memory, and it is administered orally. In the Digit Span Forward task, participants must repeat sequences of numbers in the same order, which provides an indication of their verbal short-term memory. In the Digit Span Backward task, participants reproduce number sequences in reverse order to assess verbal working memory. Memory capacity is defined as the maximum span length, which is the longest sequence that can be correctly recalled. The maximum span is 9 for the Digit Span Forward task and 8 for the Digit Span Backward task. Two trials are administered at each sequence length. Additionally, performance can be expressed as a raw score, which is calculated by adding together the number of sequences correctly recalled, with a maximum raw score of 16 for both tasks. Higher scores indicate better verbal short-term and working memory performance.Cortisol and cortisone: hair samples will be collected from the posterior vertex or nape area, where hair growth is continuous and less exposed to external contaminants. This sampling site is recommended due to its lower intra-individual variability and greater representativeness of long-term systemic hormone exposure. A small section of hair will be tied with thread near the cut end to identify the portion closest to the scalp during analysis and to prevent hair loss. Using clean scissors, the hair will be cut as close as possible to the scalp, obtaining a segment approximately 3 cm in length. This length allows for the assessment of cortisol and cortisone levels accumulated over the past three months, based on an average hair growth rate of 1 cm per month.

### Intervention

#### Experimental group.

Participants assigned to the experimental condition will receive the UP in group format. The UP is a transdiagnostic CBT intervention composed of eight modules designed to train participants in emotion regulation skills [45]. In this study these eight modules will be distributed to be applied through 12 online sessions (videocalls). The distribution of the sessions can be consulted in Table 2. The sessions will be conducted by a research team trained in the UP (Level II certification) and supervised by a clinician with Level III UP certification. In addition, treatment fidelity to the UP will be monitored throughout the course of the sessions.

**Table 2 pone.0342908.t002:** Distribution of the UP sessions.

UP modules	Sessions
1. Setting goals and maintaining motivation	1
2. Understanding emotions	2 - 3
*3. Mindful emotion awareness*	4 - 5
*4. Flexible thinking*	6 - 7
*5. Emotional behaviors*	8
*6. Facing physical sensations*	9
*7. Emotional exposures*	10 - 11
8. Relapse prevention	12

Note: the five core UP modules have been indicated in italics.

The first session will serve to introduce the program’s characteristics, to present the research team members (therapist and co-therapist) and provide an opportunity for participants to get to know each other. After this introduction, the content of the session (i.e., setting goals and maintaining motivation) will be presented. Subsequent sessions (i.e., from the second to the twelve session) will follow the same structure: during the first hour, exercises from the previous week will be reviewed. The second hour will include the introduction of the new module’s content, the practice of the corresponding module exercises, and the assignment of the exercises to be completed during the week. After each module (at the end of sessions 1, 3, 5, 7, 8, 9, 11, and 12), the true/false questions proposed in the UP will be administered to ensure that participants have correctly acquired the basic knowledge of the module.

#### Control group.

Individuals assigned to the control condition will remain on a waiting list for the 12 weeks it takes for the experimental group to receive the intervention. During this period of time, participants who are receiving follow-up for their physical health at any healthcare center may continue attending these appointments (i.e., regular visits with doctors, physicians, nurses, etc. to monitor the physical symptoms of long COVID-19). However, they will be asked not to initiate any additional psychological treatment until they have completed their participation in the study. For ethical reasons, once the post-treatment (t_2_) has been completed, participants in the control group will be offered the opportunity to join the experimental group.

Participants in both groups will be informed, both in the informed consent and also during the initial appointment with the research team, that they may withdraw from the study at any time. Likewise, the research team may recommend discontinuation if a worsening of symptoms is observed or if participants did not meet with the required procedures (i.e., attending to the sessions, responding questionnaires, providing hair samples, etc.)

### Data analysis

First, descriptive statistics of clinical psychological diagnosis, sociodemographic, and long COVID-19 symptoms will be explored to characterize the sample at baseline. Means and standard deviations for psychological measures (i.e., ODSIS, OASIS, etc.) at pre-treatment will also be calculated to provide a baseline description of our sample.

Second, the main effect of time, group and time x group interaction will be analyzed. Several linear mixed-effects models will be employed for each dependent variable to be analyzed (i.e., primary outcomes such as anxiety and depressive symptoms; secondary outcomes such as memory failures, emotional regulation difficulties, etc.). For each of these models, Time (within-subject variable; T1 vs. T2 vs. T3 vs. T4 vs. T5) and Experimental Group (between-subject variable; Experimental vs. Waitlist) will be included as fixed effects. Random slopes for participants will also be considered and included as random effects in the model. The models will have the following structure: [Dependent Variable ~ Time × Experimental Group + (1|Participant)].

In participants from the experimental group, descriptive analyses will also be conducted to assess their neuropsychological and cognitive status, as well as stress levels (hair cortisol and cortisone), prior to starting the intervention. Repeated measures ANOVAs with time as the within-subject factor will be performed to determine whether changes occur in these variables over time (i.e., after the intervention and at 3 and 12-months follow up). Exploratory correlational analyses will be conducted to examine associations between hormonal levels and other dependent variables. Subsequently, multiple linear regression analyses will be performed to determine which hormonal variables significantly predict subjective cognitive complaints, objective cognitive performance, and emotional variables, while controlling for relevant covariates (e.g., age and educational level).

Satisfaction with the intervention will be summarized using means and standard deviations derived from the satisfaction questionnaire. Additionally, adherence to the intervention will be calculated as the proportion of attended sessions relative to those scheduled.

Analyses will be conducted using the lme4 package (version lme4_1.1–13; [46]) in R statistical software (version 4.1.0; [47]) and SPSS v25.0 [48].

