### Participants

Participants will be adults residing in the Autonomous Community of Aragon (Spain) who have been diagnosed with long COVID-19 and meet criteria for at least one comorbid emotional disorder. Recruitment will take place at Hospital Royo Villanova from Zaragoza, Spain. An online dissemination campaign will also be conducted through social medial and in collaboration with the Long COVID-19 association from Aragón. Eligibility criteria to participate in the study are reported in Table 1. Participants will not be involved in the design, conduct or reporting the trial.

**Table 1 pone.0342908.t001:** Inclusion and exclusion criteria to participate in the randomized controlled trial.

Inclusion criteria	Exclusion criteria
Residing in the Autonomous Community of Aragon (Spain). Being at least 18 years old. Understanding of Spanish. Being diagnosed with long COVID-19: documented SARS-CoV-2 infection and persistence of symptoms beyond 12 weeks after the acute infection. Symptoms of depression (ODSIS≥7) and/or anxiety (OASIS≥8). Meeting the criteria for an emotional disorder diagnosis. Having access to the Internet. Signing the informed consent.	Pre-existing emotional symptoms prior to the acute SARS-CoV-2 infection. Currently receiving psychological treatment. Having a diagnosis of severe mental disorder (e.g., personality disorder, bipolar disorder, etc.). Active suicidal ideation at the time of the assessment. Individuals on psychotropic medication must maintain their dosage throughout the study, unless medically contraindicated.

Using the G*Power software [23], and taking into account the two study conditions, the five assessment points (pre-treatment, post-treatment, and follow-ups at 3, 6, and 12 months), as well as the statistical models planned for data analysis, we calculated a total sample size of 74 participants, achieving a statistical power of 90%, an alpha level of 0.05, and an effect size of 0.30. Considering an anticipated dropout rate of 20%, the required sample size is estimated at 45 participants per condition (total sample size = 90 participants).

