Despite the results of this study may have important clinical implications, we need to also acknowledge certain limitations. First, participants and researchers cannot be blinded to the intervention assignment, which may introduce expectancy effects. To minimize this potential bias, online assessments will be conducted so that the researchers are not involved in evaluating the efficacy of the intervention. Second, although sample size has been estimated to be sufficient to detect moderate effects, it may limit generalizability to broader populations or to patients with higher or lower long COVID-19 severities. Third, digital literacy of potential participants may interfere or even impede their participation in the study. For instance, participants may present difficulties to engage with the online platform to respond to the psychological assessments or they may find difficulties to engage in the online sessions through videocalls. These potential technology-related challenges will be partially mitigated by the support of the therapist who will explain the procedures for completing the assessment protocol and engaging in the online sessions. Additionally, satisfaction questions regarding the online format will also be included to capture participants’ opinion about the intervention and to evaluate whether these issues have been adequately addressed. Related with participants’ interest in this study, it is possible that some participants may show reluctance when asked to provide a hair sample. To minimize this potential concern, the research team will explain to participants that the hair sample consists of collecting only 5–6 strands from the back of the head and it will not affect their physical appearance. Finally, another potential limitation is that, for ethical reasons, participants in the control group will be offered the opportunity to join in the experimental group after completing the post-treatment assessment. Consequently, only the experimental group will be available for follow-up assessments, and comparisons between groups will be limited to the post-treatment time point.

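### The efficacy model crosses five time points with two arms although the randomised comparison ends at T2; only the T2×Group term is a valid between-arm test, and the plan does not name it as the efficacy test

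*Protocol article*

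**What the plan says.** The Data analysis section of the protocol article states that "the main effect of time, group and time x group interaction will be analyzed", and applies this to each primary and secondary outcome. The factors are given as "Time (within-subject variable; T1 vs. T2 vs. T3 vs. T4 vs. T5) and Experimental Group (between-subject variable; Experimental vs. Waitlist) will be included". The formula is "Dependent Variable ~ Time × Experimental Group + (1|Participant", that is, the full crossing with a random intercept. Nothing there limits the between-arm comparison to T1 and T2, singles out a T2 contrast, or says what happens to control records collected after crossover.

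The design is described elsewhere in the article:

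- Procedures, on controls: "they will remain on the waiting list for 12 weeks and will not receive any psychological intervention". After completing the post-treatment assessment they "will then be enrolled in the experimental group following the same procedures previously described for this condition".
- Control group: once T2 is complete, "participants in the control group will be offered the opportunity to join the experimental group".
- Discussion, limitations: "only the experimental group will be available for follow-up assessments, and comparisons between groups will be limited to the post-treatment time point".

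The sample size in the Participants section was obtained by "taking into account the two study conditions, the five assessment points (pre-treatment, post-treatment, and follow-ups at 3, 6, and 12 months" and so on, giving 74 evaluable participants for 90% power, alpha 0.05 and an effect size of 0.30, and 90 enrolled.

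**The concern.** The model and the design disagree. The model assumes an Experimental and a Waitlist group at all five assessments. The design has an untreated waitlist only at T1 and T2. At T3–T5 the Waitlist cells are either empty, as the Discussion says, or filled with people who have since received UP, which the Procedures wording could allow. In neither case do T3–T5 contain a comparison of UP with no treatment.

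This matters because the trial is a superiority RCT and the plan lists three omnibus effects without saying which one answers the superiority question. A time effect is not a between-arm comparison. A five-wave group effect is either undefined or diluted. The one randomised contrast is a single term inside the interaction. With the efficacy test unnamed and allocation known to the researchers, the choice among these effects is left open until the results are seen. The sample size also counts all five assessments, so the stated 90% power may not apply to the comparison the trial can make.

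**Working it through.** **1. The plan's sample size.** Inputs from Participants: two arms, five assessments, effect size 0.30, alpha 0.05, power 90%, N = 74. The effect-size metric and the within-person correlation ρ are not stated. Assumed here: Cohen's f = 0.30 and ρ = 0.5.

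Between-group main effect in a repeated-measures ANOVA with m assessments: λ = f²·N·m / [1 + (m − 1)ρ], with 1 and N − 2 df.

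- m = 5, N = 74: λ = 0.09 × 74 × 5 / 3 = 11.1, power 90.8%. At N = 72 power is 89.99%, so 74 is the smallest even total that reaches 90%.
- Alternatives tried do not give 74. The within-between interaction with m = 5 needs 10–26 for ρ from 0.8 to 0.3; two means with d = 0.30 need 468.

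So 74 is reproduced as a group main effect averaged over five waves. Because the metric and ρ are unstated, this is an inference.

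**2. No control data at T3–T5 (Discussion).** The 5 × 2 model has 10 fixed-effect columns: intercept, 4 time, 1 group, 4 interaction. The filled cells are 5 experimental and 2 waitlist, 7 in all, and the design matrix has rank 7.

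| Effect | Estimable? |
|---|---|
| Group difference at T1 | yes |
| T2×Group (arm difference in change from T1 to T2) | yes |
| T3×Group, T4×Group, T5×Group | no |
| Group effect averaged over T1–T5 | no |

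The planned 4-df interaction therefore reduces to 1 df.

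**3. Crossed-over controls kept as Waitlist.** Assume a difference of 0.60 SD at T2 and equal benefit in both arms once controls are treated. The arm differences at T1–T5 are then 0, 0.60, 0, 0, 0, with mean 0.60/5 = 0.12 SD. There are n = 37 per arm.

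- Group main effect: λ = 0.12² / [(2/37)(1 + 4ρ)/5]. For ρ = 0.3, 0.5 and 0.8, λ = 0.61, 0.44 and 0.32, and power is 12%, 10% and 9%.
- Interaction, 4 df: the squared deviations of the differences from their mean sum to 0.48² + 4 × 0.12² = 0.288. At ρ = 0.5, λ = (0.288/2) × 37/(1 − 0.5) = 10.66, power about 74%.
- T2×Group: at ρ = 0.5, λ = 0.36 / [(2/37) × 2 × 0.5] = 6.66, power about 72–73% depending on the error df.

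In 100 simulated trials with a true T2 effect of 0.60 and ρ = 0.5, the T2×Group estimate averaged 0.61 both with and without control follow-up data. The averaged group effect, with crossed-over records kept, was 0.11.

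**4. Power for what the design can compare.** Same formula, f = 0.30, ρ = 0.5, N = 74:

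- averaged over T1–T2 (m = 2): λ = 0.09 × 74 × 2 / 1.5 = 8.88, power 83.6%. This still credits the difference to T1, where randomisation makes the expected difference zero;
- T2 alone, unadjusted (m = 1): λ = 0.09 × 74 = 6.66, power 72.1%;
- T2 adjusted for baseline: λ = 0.09 × 74 / (1 − ρ²), power 76.1%, 83.6% and 94.6% for ρ = 0.3, 0.5 and 0.7.

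**The case against.** The strongest reply is that the stated formula already contains the valid test. T2×Group is estimable with or without control follow-up data, and the Introduction's hypothesis of greater improvement than control is a difference in change, hence an interaction. The Introduction also places the improvements at post-treatment and treats follow-up as maintenance, and the Discussion concedes that arms can be compared only at T2. On this reading the intent is clear and one sentence is missing. All of this stands, and it limits the point to the effects named above.

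A reader might go further and infer that the model offers no valid between-arm comparison, or that the trial has only about 10% power. The document does not support either. The T2×Group term is a clean randomised contrast. The figure of about 10% belongs only to the five-wave group main effect, and it needs treated controls to stay in the analysis as Waitlist, which the Discussion's statement on follow-up excludes. In that same scenario the interaction keeps about 74% at ρ = 0.5. Nor do the Procedures say that control follow-up data are absent; only the Discussion does, and the Control group section words crossover as an offer.

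A multiplicity rule for the two primary scales, baseline adjustment, and separate rather than joint models may properly be left to an analysis plan that is not shown. The reply does not remove the conflict itself: the Data analysis section states a specific model and specific tests that the design described in the same article cannot support.

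**Conclusion.** The point holds in this limited form. As written, the Data analysis section tests a five-wave group effect and T3–T5 interactions that are not estimable under the Discussion's account of the data, or that compare treated with treated if crossed-over records are kept. The rank result (7 of 10) needs no numerical assumption. The 0.12 SD and 9–12% figures rest on an assumed effect of 0.60 SD at T2 only, equal benefit in both arms after crossover, and correlations of 0.8 to 0.3. A valid efficacy test exists in T2×Group, but the plan does not make it the efficacy test.

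The power consequence is likely but inferred. If f = 0.30 and ρ = 0.5 were the inputs behind 74, the stated 90% belongs to a five-wave average, and the T2 comparison has 72.1% unadjusted. Baseline adjustment recovers part or all of the loss, depending on the correlation.

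**What to change.** In the Data analysis section:

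- Name the arm difference at T2 on ODSIS and OASIS as the between-group efficacy test, in all randomised participants by allocated arm. It may come from a T1–T2 model or from a pre-specified T2 contrast in the mixed model; either is sound.
- Drop the five-wave group main effect and the T3–T5 interactions as between-arm tests.
- Analyse T3–T5 as within-arm maintenance in participants randomised to UP, and label it uncontrolled.
- State that controls' post-crossover records do not enter the efficacy contrast.

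In the Participants section, restate the power for the T2 contrast, with the effect-size metric and the assumed correlation.

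The analysis changes are rewording and need no new data. The cost is a stated power that is probably less favourable than 90%, and between-arm claims confined to T2, which the Discussion already accepts.
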